### Sample size {14}

There is no widely accepted and established minimal clinically significant difference for the primary outcome, WEMWBS. It has been suggested that a change of three or more points is likely to be important to individuals but different statistical approaches provide different estimates ranging from three to eight points (WEMWBS user guide [22]). There is also variation in the standard deviation of the WEMWBS with estimates ranging from 6 to 10.8 [30] with the pooled estimate of 10 across all studies. Assuming 90% power, 5% 2-sided statistical significance, mean difference of 4 points on WEMWBS and a standard deviation of 10, 266 participants are required. Preliminary figures from The Hampton Trust’s skills/attitudes workshops for domestic abuse (RADAR intervention) suggests a drop-out rate of approximately 15%. Conservatively, assuming a 20% attrition rate, 334 participants would need to be recruited and randomised.

### Recruitment {15}

The study population represents a vulnerable group with complex and overlapping health and social needs. They may include disadvantaged young adults, faced with previous and continuous adversity, such as unemployment, substance misuse and/or exposure to abuse. Our process for recruitment acknowledges that engaging with this target population is likely to be challenging.

The first 6 months of recruitment was run as an internal pilot to assess whether continued progression into the full trial was appropriate. According to police estimates at the start of recruitment, an average of 23 individuals would be eligible to receive the Gateway intervention each month once all the sites are recruiting.

Participants who consent at Stage 1 are now contacted by a member of the Police Gateway Team based at Southampton Central Police Station within a week of recruitment or as near to that time as practicable. The Police Gateway Team may attempt contacting the participants on more than one occasion and will also check if HC has received any updates on participants’ contact details should initial attempts be unsuccessful.

Participants are emailed a copy of the Questionnaire Study leaflet and a link to the Questionnaire Study video. The email also contains a study phone number and email address, to enable participants to contact the researchers directly.

The researchers attempt to contact participants in time to arrange the week 4 interview. The researchers provide participants with further information about the study and attempt to arrange the first telephone interview. A degree of flexibility is exercised, as dictated by the timing of the receipt of participants’ details following randomisation, and the availability of the participant and/or researchers.

The Police Gateway Team monitor recruitment on a daily basis, contact investigators where they see a case may be eligible to remind them about the Gateway caution and study, and discuss with investigators where a potential participant has been missed. All the Gateway and study documentation and information are readily available on the HC computer system. A variety of methods are used to raise and maintain awareness of the Gateway study within HC, such as computer screen savers, notices in police station offices and newsletter articles from the Deputy Chief Constable. Refresher training will be undertaken where necessary.

## Assignment of interventions: allocation

### Sequence generation {16a}

Participants will be allocated using simple randomisation with a 1:1 allocation ratio. The allocation sequence will be created using computer-generated random numbers in Alchemer using a randomisation sequence approved by the trial statistician. The system was tested and verified by York Trials Unit (YTU) data management and the trial statisticians during the training of police investigators, prior to the start of recruitment to the study.

### Concealment mechanism {16b}

Alchemer automatically generates and records the random allocation when a police investigator enters details for an eligible participant. It is not possible for investigators to predict or influence the allocation.

### Implementation {16c}

The allocation is generated when a police investigator enters the details of a potential participant, and they meet the eligibility criteria. The allocation of Gateway conditional caution or an alternative conditional caution or prosecution is displayed on the screen. The police investigator then informs the participant of the allocation and proceeds with disposal using the allocated intervention. A similar method for randomisation was adopted in an RCT of domestic abuse perpetrator intervention (CARA) conducted in Southampton Police District, where they were able to successfully recruit a similar population group (*n* = 293) [31].

## Assignment of interventions: blinding

### Who will be blinded {17a}

Consent for eligibility screening, Gateway consideration, sharing of contact details and the randomisation is undertaken by the police investigators, none of whom are involved in data collection for the study.

UoS Research team members involved in obtaining Stage 2 consent and data collection will be blinded as far as possible to the randomised group. The CRFs include a tick box for the researcher to indicate whether they believe blinding was compromised during assessment, or other communications such as when booking appointments, and if so which of the allocation groups they believe the participant to be in.

The statistician will not be blinded to treatment allocation.

### Procedure for unblinding if needed {17b}

No safety unblinding is foreseen in this study.

## Data collection and management

### Plans for assessment and collection of outcomes {18a}

Study outcome data will be recorded in paper Case Report Forms (CRFs) by researchers experienced in undertaking interviews. All three of the outcome data collection CRFs include WEMWBS, SF-12, AUDIT and ADIS measurement tools. Demographic data will also be collected in a CRF.

Following Stage 2 consent, the UoS researchers will read out the questions and answer options as set out in the relevant CRF. Guidance may be given if a question is not understood or requires further clarification. The researcher will hand-write the responses in the CRFs. Each CRF will be identified with a unique participant ID, signed and dated by the researcher and posted to YTU data management in a pre-paid envelope. The UoS researchers will track completion of each interview and CRF and YTU will track CRFs received and the date of receipt.

A participant may be reported as withdrawing from the study either by a researcher or a member of the Gateway police team using a Change of Status CRF. The Police Gateway Team may also report a participant withdrawing from the Gateway intervention.

A Case Management System (Huddle) is maintained centrally by Southampton Police as a key for linking the various sources of data for individuals together. For the purposes of analysis, data will be pseudonymised, and for subsequent reports and publications, the data will be wholly anonymised. For the purposes of ongoing data management, once randomised, individual participants will be identified using their unique study identification number including the site identifier they were recruited from.

Trial data and study files will be handled in accordance with Good Clinical Practice (GCP) principles, the appropriate data management procedures and YTU Standard Operating Procedures (SOPs).

### Plans to promote participant retention and complete follow-up {18b}

Early contact with participants by the Police Gateway Team and then the UoS researchers will be made to check that the telephone number given is active and to establish engagement.

Based on HRA guidance and advice from our Patient and Participant Involvement (PPI) representative, vouchers to the value of £30 for completion of week 4 CRFs, £40 for week 16 and £50 for a year 1 will be offered. A variety of methods to ensure the secure delivery of vouchers will be put in place to reduce selection bias, boost recruitment of those young adults with unstable living arrangements, without a bank account or lacking access to email or the Internet, who may otherwise not be inclined to participate.

### Data management {19}

#### Data entry and management

All staff involved in handling study data have been trained in data protection and data security. Trial data will be stored and transferred following YTU SOPs. Data will be processed according to trial-specific procedures and the Data Management Plan, all kept in the Trial Management File (TMF).

Paper CRFs received by YTU data management team will be scanned into OpenText Teleform, a secure, form processing software application that minimises the risk of data entry errors. Data queries will be raised with the UoS researchers and documented.

A Case Management System (Huddle) is maintained by the Police Gateway Team as a secure central location for data and document storage and sharing in line with the study Information Sharing Agreement. For the purposes of ongoing data management, once randomised, individual participants will be identified using their unique study identification number.

#### Data storage and archiving

Each site will hold data according to the UK General Data Protection Regulation (GDPR) and Data Protection Act (Great Britain 2018); data storage will be regularly reviewed to ensure compliance. Following Stage 2 consent, personal data and special category personal data will be processed in connection with this study under the legal basis of Article 6(1)(e) and Article 9(2)(j) of the UK General Data Protection Regulation (GDPR), for processing for the performance of a task carried out in the public interest, and as necessary for archiving purposes in the public interest, scientific or historical research purposes or statistical purposes, with Article 9(2)(j) operating in conjunction with the safeguard requirements set out in Article 89(1) of the GDPR.

All study files will be stored in accordance with GCP guidelines. Study documents (paper and electronic) will be retained in a secure (kept locked when not in use) location for the duration of the study. All essential documents, including source documents, will be retained for a minimum period of 10 years after study completion. The separate archival of electronic data will be performed at the end of the study, to safeguard the data for the period(s) established by relevant regulatory requirements. All work will be conducted following the University of York (UoY) Data Protection Policy [32].

### Confidentiality {27}

Participants will be assigned a unique identification number for use on consent forms, CRFs and other participant-specific records. Personal data will only be used when specific consent for its use for research purposes has been given to the investigator by the participants. Details will then be stored securely in the police research Case Management System (Huddle) for selective sharing with the research team only.

Electronic copies of Stage 1 and Stage 2 consent forms will be held securely in Huddle with limited and password-protected access. Personal information will not be released, except as necessary for the study and monitoring purposes.

All information provided for the purposes of this study will be kept strictly confidential. However, if a participant discloses information that may mean the future harm of another individual or relate to an offence for which they have not been charged, then the researchers are required to break that confidence by law. Examples of such disclosures are outlined in the Stage 2 PIS to make this risk clear to potential participants.

The research teams at the UoY and UoS will be the only individuals with access to study data. Primary data will be pseudonymised using the participant unique ID. A link back to the participant details will only be possible through the Document Management System (Huddle) and only UoS have access to shared personal contact details, in line with Stage 1 consent.

A police data analyst will ensure that all routinely collected police data is pseudonymised, using only the participant unique ID, before being transferred securely to the Universities. To access police data, a confidentiality agreement between the respective parties has been put in place.

## Statistical methods

### Statistical methods for primary and secondary outcomes {20a}

A detailed statistical analysis plan (SAP) will be agreed with the TMG and SSC/DMEC before all of the data have been collected. Amendments to the SAP will be agreed and clearly stated and justified. Analyses will be carried out using Stata v17 or later and follow the principles of intention-to-treat with outcomes analysed according to randomised group unless otherwise specified. Parameter estimates will be presented with associated 95% confidence intervals and *p* values, and significance testing will be two-sided at the 5% level unless otherwise stated.

The primary analysis will compare WEMWBS between treatment groups at 12 months and will be analysed using a covariance-pattern mixed-effect linear regression model, including assessments at 4 weeks, 16 weeks and 12 months post-randomisation, and treating participants as a random effect in order to account for repeated measurements amongst participants. Treatment group, time, group by time interaction, the total of the number of Record Management System (RMS) incidents and the number of Police National Computer (PNC) convictions 1 year pre-randomisation, age at randomisation, Index of Multiple Deprivation quintile at randomisation, pandemic time period and standard of usual process available will be adjusted for as fixed effects. If feasible, recruiting site will be included as a random effect. Pandemic time period refers to whether the follow-up took place before, during or after the COVID-19 pandemic, while standard of usual process available refers to the variation in the types of caution available during the pandemic. The inclusion of these two covariates reflects the guidance provided by Cro and colleagues for handling missing outcome data in randomised trials affected by the pandemic [33]. The treatment effect estimate at 12 months will be presented in the form of an adjusted mean difference, alongside the associated 95% confidence interval and *p* value. The treatment effect estimates at 4 weeks and 16 weeks will be presented in a similar manner as secondary outcomes.

The continuous secondary outcomes will be analysed in a similar manner to the primary outcome. Binary secondary outcomes will be analysed using a covariance-pattern mixed-effect logistic regression model and secondary outcomes classed as count data will be analysed using Poisson or negative binomial regression models. The models will adjust for the same fixed and random effects as the primary analysis.

### Interim analyses {21b}

There are no planned interim analyses for this study.

### Methods for additional analyses (e.g. subgroup analyses) {20b}

For the primary outcome, a subgroup analysis will be carried out comparing participants 18–21 years old to participants 22–24 years old (chosen on the basis that social services support care leavers up to 21 years old). The subgroup analysis will be carried out by repeating the primary analysis model with the addition of an interaction term between treatment group and subgroup.

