### Outcomes {12}

#### Primary outcome measure

The primary outcome measure is the Warwick-Edinburgh Mental Well-being Scale (WEMWBS) at 12 months. This is used to measure health and well-being amongst study participants. WEMWBS is a 14-item self-reported questionnaire that addresses mental health and well-being and has established valid reliable psychometric properties in adolescent populations [21, 22]. Compared to other well-being indices, WEMWBS was tested for response bias and showed low correlation with both subscales of the Balanced Inventory of Desirable Responding: Impression Management (*p* = 0.18*) and self-deception (*p* = 0.35**), which make it suitable for self-report [23]. Participants will self-report WEMWBS at 4 weeks, 16 weeks and 1 year post-randomisation (**p* < 0.05, ***p* < 0.01).

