#### Secondary outcome measures

The following are the secondary outcome measures:
WEMWBS at 4 and 16 weeks post-randomisation.The SF-12 will be used to report health status. The 12 items of the SF-12 provide a representative sample of the content of the eight health concepts [24] and the various operational definitions of those concepts, including what respondents are able to do, how they feel and how they evaluate their health status.Risky alcohol use will be measured using the Alcohol Use Disorders Identification Test (AUDIT). The AUDIT tool is a simple screening tool that is used to identify the early signs of hazardous and harmful drinking and mild dependence. AUDIT has been validated amongst an adolescent [25, 26] and collage age population [27].Drug use will be measured using the Adolescent Drug Involvement Scale (ADIS). The ADIS was deemed most appropriate, as it captures recent/current use, and has been validated within this population age group [28].Reoffending type and frequency through access to routine data: police records will be used to examine the type and frequency of the trigger and subsequent offences up to 1-year post-randomisation.Data on resource use, including access to primary and secondary care health services and social care, will primarily be used to inform cost consequence analysis. Data will be obtained through self-reported responses to questions in the CRFs based on the customised Client Service Receipt Inventory [29].

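### The age-subgroup model adds one treatment-by-subgroup term to a three-visit model, so it estimates a visit-weighted average rather than the subgroup effect on WEMWBS at 12 months

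*Protocol article*

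**What the plan says.** Three parts of the protocol article bear on this.

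- **Outcome.** The section Primary outcome measure states: "The primary outcome measure is the Warwick-Edinburgh Mental Well-being Scale (WEMWBS) at 12 months". The list under Secondary outcome measures includes "WEMWBS at 4 and 16 weeks post-randomisation", so the earlier scores are separate, secondary outcomes.
- **Primary model.** Section {20a} fits one repeated-measures model, "including assessments at 4 weeks, 16 weeks and 12 months post-randomisation". Its fixed effects include "Treatment group, time, group by time interaction", and the result is read off at one visit: "The treatment effect estimate at 12 months will be presented in the form of an adjusted mean difference".
- **Subgroup model.** Section {20b} says: "For the primary outcome, a subgroup analysis will be carried out comparing participants 18–21 years old to participants 22–24 years old". The method is "repeating the primary analysis model with the addition of an interaction term between treatment group and subgroup". It mentions no term crossing subgroup with time and no contrast at a named visit.

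**The concern.** The subgroup analysis is labelled as being for an outcome at one visit, but the added term has no visit attached to it. In a model with three visits, a lone treatment-by-subgroup coefficient is common to all of them. The group-by-time term already in the model does not help: it lets the overall treatment effect change between visits, but not the gap between the two age groups.

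The trial's timetable gives no reason to presume a constant gap. The week 4 assessment falls before the second workshop (weeks 5–6), week 16 falls at about the end of the caution, and 12 months is well after it. If effect modification changes over that period, the planned test can dilute a real 12-month difference, or report as a 12-month finding one that existed only early on.

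**Working it through.** **The plan's own figure.** Section {14} states: "Assuming 90% power, 5% 2-sided statistical significance, mean difference of 4 points on WEMWBS and a standard deviation of 10, 266 participants are required". Under the normal approximation, 2 × (1.960 + 1.282)² × 10² / 4² = 131.4, so 132 per arm (264). The noncentral t calculation gives 133 per arm (266, power 0.901). Inflating, 133 / 0.8 = 166.25, so 167 per arm (334). The sample size reproduces. The article gives no figure for the subgroup analysis.

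**Inputs.** From the documents: 266 analysed, SD 10, 1:1 allocation, three visits. Assumed: half of participants in each age group, complete data, and a range of within-person correlations, since the article names no covariance structure. The first-order autoregressive cases treat visits as equally spaced. The subgroup main effect is included in both models.

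**What the two-way term estimates.** Let δ = (δ4, δ16, δ12m) be the true differences in treatment effect between the age groups at the three visits, and Σ the 3 × 3 within-person covariance matrix. Under generalised least squares the coefficient is the sum of w_t × δ_t, with weights w = Σ⁻¹1 / (1′Σ⁻¹1). Adding subgroup by time without the three-way term leaves this unchanged.

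**Standard errors.** There are four treatment-by-age cells of 266 / 4 = 66.5, so the variance multiplier is 4 / 66.5 = 0.0602.

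- 12-month contrast from the three-way model: √(0.0602 × 100) = 2.45.
- Two-way term: √(0.0602 / (1′Σ⁻¹1)). Under compound symmetry, 1 / (1′Σ⁻¹1) = 100(1 + 2ρ) / 3. With ρ = 0.5 this is 66.7, giving SE 2.00.

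**Rejection probability.** Φ(|e|/SE − 1.96) + Φ(−|e|/SE − 1.96), where e is the expected estimate. For the 12-month contrast with a true value of 4, 4 / 2.45 = 1.63, giving 37%.

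**Results.** Each scenario lists the true differences at week 4 / week 16 / 12 months. Cells show the expected estimate, with the rejection probability in brackets.

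| Model and correlation | Weights | SE | 0/0/4 | 4/4/0 | 4/4/4 |
|---|---|---|---|---|---|
| Two-way, compound symmetry 0.3 | 0.33/0.33/0.33 | 1.79 | 1.33 (11.6%) | 2.67 (31.9%) | 4.00 (60.8%) |
| Two-way, compound symmetry 0.5 | 0.33/0.33/0.33 | 2.00 | 1.33 (10.2%) | 2.67 (26.5%) | 4.00 (51.5%) |
| Two-way, compound symmetry 0.7 | 0.33/0.33/0.33 | 2.19 | 1.33 (9.3%) | 2.67 (22.9%) | 4.00 (44.6%) |
| Two-way, autoregressive 0.5 | 0.40/0.20/0.40 | 1.90 | 1.60 (13.4%) | 2.40 (24.4%) | 4.00 (55.8%) |
| Two-way, autoregressive 0.7 | 0.43/0.13/0.43 | 2.11 | 1.74 (13.1%) | 2.26 (18.9%) | 4.00 (47.5%) |
| Two-way, unstructured 0.7 (wk 4–16), 0.4 (wk 4–12 mo), 0.5 (wk 16–12 mo) | 0.36/0.21/0.43 | 2.02 | 1.71 (13.6%) | 2.29 (20.5%) | 4.00 (50.8%) |
| 12-month contrast, all cases | 0/0/1 | 2.45 | 4.00 (37.1%) | 0.00 (5.0%) | 4.00 (37.1%) |

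If the difference changes sign over time (2/2/−4), the two-way term is expected between 0.00 and −0.61 instead of −4.

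**Sensitivity to the age split.** With complete data the weights do not depend on the split. If 3/7 were in the older group (three of the seven single years of age), both standard errors would rise by √(0.25 / (3/7 × 4/7)) = 1.01.

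**The case against.** The strongest reply is that section {20b} is one sentence in a condensed article. A detailed SAP is promised, and the sentence names the primary outcome. On that reading, repeating the primary model carries its 12-month contrast along, with the full list of terms left to the SAP. This is arguable and lowers the severity. It does not dispose of the point, because the article states a model instead of deferring it. An SAP that follows the sentence literally inherits the problem, and one that adds the three-way term departs from it.

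A second reply is that the two-way term is biased for the 12-month effect only if effect modification varies over time. That is true. Under a constant difference it is the better estimator, with a smaller standard error. But constancy is an assumption, and the article does not make it.

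Third, the recommended contrast is itself weak: about 37% power for a 4-point difference. That also stands. The correction makes the analysis answer its stated question; it does not make it well powered.

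A reader might also infer that the subgroup main effect is left out, so that a non-linear age effect could load onto the interaction. The text does not support this. It is silent on the main effect, adding an interaction conventionally brings its component terms, and the discrepancy above arises with the main effect included.

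**Conclusion.** The point holds, at moderate severity. As written, the subgroup term gives the 12-month visit a weight of about 0.33 to 0.43 and draws the rest from visits that the protocol classes as secondary. It matches the 12-month subgroup effect only under constant effect modification. Otherwise, in the scenarios examined, a 4-point difference confined to 12 months shrinks to between 1.3 and 1.7, and one absent at 12 months is declared in 19–32% of trials.

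These sizes rest on the assumed correlations, even age split and complete data, and on differences chosen to vary strongly between visits. Incomplete data would change the weights. The documents do not indicate which pattern over time is likely, so the figures show what could happen and are not a forecast.

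A reader might go further and conclude that the primary result is compromised. It is not: the primary model contains the group-by-time term that it needs, and the sample size reproduces. The effect is confined to one subgroup analysis for which the trial was not sized and to which the article attaches no decision rule.

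**What to change.** In section {20b}, and in the SAP to match, state that the primary model is repeated with subgroup by time and treatment by subgroup by time added, together with the usual lower-order terms. State also that the treatment-by-subgroup contrast at 12 months is reported with its 95% confidence interval and p value.

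If an interaction averaged over visits is what the team wants, the text should say so, state the constancy assumption, and not present the result as one for the 12-month outcome. The choice should be made before the data are analysed, since choosing between the two tests afterwards would be data-driven.

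The cost is a sentence and a few model terms. The statistical price is a wider interval for the interaction: SE 2.45 against 1.79 to 2.19 under the assumptions above.
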